#### Feasibility

Feasibility outcomes include recruitment rate, retention rate, intervention adherence, intervention fidelity, and safety. The definition and criteria for success for each feasibility outcome are presented in Table 1. Reasons for declining to participate in the study, and reasons for withdrawing from the study after providing consent, will also be recorded in a Consolidated Standards of Reporting Trials (CONSORT) flowchart.

**Table 1 Tab1:** Feasibility outcomes for this study

Outcome	Definition
Recruitment rate	The proportion of eligible patients who are approached and give informed consent to participate
Retention rate^a^	The proportion of patients who consent to take part in the study and complete the FACT-Hep questionnaire at both baseline and 10-week follow-up
Intervention adherence^b^	i) The mean proportion of exercise sessions attended by patients (assessed by attendance records kept by the intervention facilitator) ii) The mean proportion of exercise sessions completed at or above a moderate intensity, assessed via RPE (rating of ≥ 3 on the 10-point scale)
Intervention fidelity	Assessed by a research team member attending a 10% sample of the virtual exercise sessions using a standardised checklist to check whether the sessions are delivered in accordance with the protocol
Safety	The number and type (i.e. serious or non-serious) of adverse events that are related or possibly related to the intervention or study procedures

^a^The Functional Assessment of Cancer Therapy-Hepatobiliary (FACT-Hep) questionnaire was chosen for the assessment of retention rate because this is likely to be our primary outcome for a subsequent randomised controlled trial

^b^Adherence to the intervention will be evaluated only in patients who complete the study, defined as patients who complete the FACT-Hep questionnaire at both baseline and 10-week follow-up

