### Sample size

There are no clear guidelines on sample size requirements for non-randomised feasibility trials. Thus, our sample size is based on the minimum number of patients the research team considers sufficient to achieve the key aims of the feasibility study and the number that is achievable to recruit within a 6-month period [48]. Based on recruitment to ongoing studies at NuTH with similar participant eligibility criteria (e.g. ISRCTN16680540), we expect that at least three eligible patients per week will be identified. Assuming that 30% of eligible patients provide consent (which is a conservative estimate based on the mean recruitment rate in similar studies [49]), we will recruit at least 20 patients in a 6-month recruitment period. We consider this number of patients sufficient to provide sufficient information on feasibility and acceptability.

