### Criteria for success

Based on a systematic review of recruitment, retention, and exercise adherences rates in patients with advanced cancer [49], this feasibility trial will be deemed successful if the following criteria are met:≥ 40% of eligible patients provide written consent to take part in the feasibility trial.≥ 70% of patients attend at least 14 out of 20 exercise sessions.≥ 75% of patients complete the FACT-Hep questionnaire at baseline and 10-week follow-up.No serious adverse events are attributable to the intervention or study procedures.

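### The only adherence denominator the protocol states is FACT-Hep completers, while the success criterion uses a different adherence statistic and names no denominator

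*Protocol article*

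**What the plan says.** The Outcomes section makes feasibility the primary outcome, and Table 1 (Feasibility) defines its components. Adherence has two parts, both means: "The mean proportion of exercise sessions attended by patients", and "The mean proportion of exercise sessions completed at or above a moderate intensity, assessed via RPE". Footnote b applies to both: "Adherence to the intervention will be evaluated only in patients who complete the study", where completing means having a FACT-Hep questionnaire at baseline and at the 10-week follow-up. That is the same event by which Table 1 defines retention.

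The Criteria for success section lists four conditions for calling the trial successful. The adherence condition is "≥ 70% of patients attend at least 14 out of 20 exercise sessions". It counts patients over a cut-off instead of averaging sessions, and it does not say which patients form the denominator. Neither of Table 1's two means has a threshold there.

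The two data sources are independent. Attendance is logged by the facilitator at each session (Table 1; Exercise intervention). FACT-Hep is a paper form that patients take home and post back (Patient-reported outcome measures).

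**The concern.** Returning FACT-Hep at 10 weeks happens after consent and after the programme. Patients who stop because the sessions are too demanding, their symptoms fluctuate or the technology fails are plausibly the least likely to return it. A completers-only rule removes them from the measure meant to show whether patients can keep up with the programme. It also discards a patient who attends all 20 sessions but never posts the form.

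Adherence is one of four conditions for success on the primary outcome, and the result is meant to shape a later randomised trial. Because the success criterion names no denominator, the same attendance data can pass or fail depending on whether the footnote is carried over. That choice should not be left until the results are known.

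**Working it through.** **Inputs.** From the protocol: 20 patients (Sample size); retention threshold 75% and adherence threshold 70% of patients at 14 or more of 20 sessions (Criteria for success); completers-only rule (Table 1, footnote b). Assumed, because the protocol gives no value: the true retention rate, the true share of completers reaching 14 sessions, and that no non-completer reaches 14 sessions.

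**The plan's own figure.** The Sample size section states "we expect that at least three eligible patients per week will be identified" and "Assuming that 30% of eligible patients provide consent". Over 24 weeks, 3 × 24 × 0.30 = 21.6; over 26 weeks, 3 × 26 × 0.30 = 23.4. Both agree with "we will recruit at least 20 patients in a 6-month recruitment period", so n = 20 is used below.

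**Step 1: smallest passing result.** Retention needs 0.75 × 20 = 15 completers. On completers, adherence needs the smallest whole number at or above 0.70 × 15 = 10.5, which is 11, and 11/15 = 73.3%. As a share of all consented, 11/20 = 55%. On all consented, adherence needs 0.70 × 20 = 14 patients. The gap is 3 patients, or 15 percentage points. Without rounding, the floor is 0.75 × 0.70 = 52.5%.

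**Step 2: other numbers of completers (n = 20).**

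| Completers | Needed on completers | Share of all 20 |
|---|---|---|
| 15 | 11 | 55% |
| 16 | 12 | 60% |
| 17 | 12 | 60% |
| 18 | 13 | 65% |
| 19 | 14 | 70% |
| 20 | 14 | 70% |

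The two denominators require the same count once 19 or more are retained.

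**Step 3: chance of passing.** Let completers C ~ Bin(20, r) and, given C, adherent completers A ~ Bin(C, a). On completers, retention and adherence are both met when C ≥ 15 and A ≥ 0.70 × C. On all consented, both are met when C ≥ 15 and A ≥ 14. Exact binomial sums give:

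| r | a | Overall r × a | Both met, completers | Both met, all consented |
|---|---|---|---|---|
| 0.75 | 0.70 | 52.5% | 31.7% | 8.7% |
| 0.75 | 11/15 | 55% | 39.0% | 12.8% |
| 0.80 | 0.75 | 60% | 56.0% | 24.8% |
| 0.80 | 0.80 | 64% | 68.1% | 37.6% |

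For r = 0.75 and a = 11/15, the adherence criterion alone is met with probability 63.0% on completers and 13.0% on all consented. The joint figures are the relevant ones, because retention must also be met.

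**Step 4: mean against cut-off.** Suppose 15 completers. If 11 attend 14 sessions and 4 attend none, mean attendance is (11 × 14)/(15 × 20) = 154/300 = 51.3%, yet the criterion passes at 73.3%. If 10 attend 20 and 5 attend 13, the mean is (200 + 65)/300 = 88.3%, yet the criterion fails at 10/15 = 66.7%. These are constructed extremes. They show that the Table 1 outcome does not determine the decision.

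**The case against.** The strongest reply is that the success criterion says only patients, and footnote b sits on a Table 1 row that defines a different statistic. If all consented patients are meant, 14 of 20 are needed and the 55% pass disappears. This stands: a reader might infer that the trial is set to pass with barely half of patients treated, but the document does not establish that footnote b governs the criterion. What remains is that the footnote is the only adherence denominator stated, and the two readings can give opposite verdicts on the same data.

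Second, dropout already counts against retention, which is defined over consented patients and must also be met. This limits the problem, and it is why the joint probabilities are used. A gap of about 26 percentage points remains in the main illustration. Recording reasons for dropout and non-adherence is useful, but does not enter the pass/fail calculation.

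Third, the direction of bias is not certain. Full attenders who do not return the form push adherence the other way. Nor does attending fewer than 14 sessions mean that a patient received nothing. Both points stand.

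Fourth, a reader might infer from the mean/cut-off mismatch that the plan could reach two conflicting decisions. It cannot, because no threshold is set on the mean. Reporting a mean beside a cut-off is ordinary; the defect is only that the decision statistic is not the one defined as the outcome.

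Finally, the thresholds come from a cited systematic review that is not available here, so the denominator behind the 70% is unknown. This stands and is carried into the fix.

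**Conclusion.** The concern holds in this form: the protocol states a completers-only rule for adherence, decides success on a different adherence statistic, and does not say whether the rule carries over. If it does, the adherence bar at n = 20 can fall from 14 patients to 11, or 55% of those consented. That is the boundary case: exactly 15 completers, exactly 11 of them adherent, and no non-completer reaching 14 sessions. In the illustration with true rates of 75% and 73%, the chance of meeting both criteria is about 39% rather than 13%. These probabilities rest on assumed rates and on the same non-completer assumption. They cover retention and adherence only; overall success also needs the recruitment and safety criteria. Upward bias is likely but not certain. This should be settled before results are seen, because the denominator alone can change a success verdict on the primary outcome.

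**What to change.** Remove the completers-only restriction for attendance. In both Table 1 and Criteria for success, define the decision statistic as the proportion of all consented patients who attend at least 14 of the 20 sessions according to the facilitator's register, counting sessions after withdrawal as not attended. Report mean attendance and completers-only adherence as secondary descriptions. State separately which patients the intensity measure covers, since footnote b applies to it too.

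The cost is a few lines of text and no new data, because the register does not depend on FACT-Hep. The adherence figure will probably be less favourable. Keeping 70% on the wider denominator raises the bar compared with the completers reading, so the sponsor should confirm that the threshold is intended for all consented patients, or justify another, before results are known.

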#### Physical function

Measures of physical function and mid-upper arm circumference will be assessed during standard of care visits to the outpatient liver cancer clinic at the treating hospital. Physical function will be assessed with the Short Physical Performance Battery (SPPB) and the Liver Frailty Index (LFI). The SPPB is a composite measure of balance, chair stands, and gait speed [33]. Each test is assigned a categorical score from 0 (worst performance) to 4 (best performance) according to standardised criteria, and a total score from 0 to 12 is obtained by summing the scores from the three tests. Higher scores in the SPPB reflect better physical function.

The LFI is a composite measure of hand grip strength, chair stands, and balance [34] and is calculated according to the following formula:$$LFI=\left(-0.330\times sex\ adjusted\ grip\ strength\right)+\left(-2.529\times number\ of\ chair\ stands\ per\ second\right)+\left(-0.040\times total\ balance\ time\right)+6$$

Grip strength is converted into sex-specific z-scores before being entered into the formula [34]. Total balance time is the sum of the three balance tests in seconds (maximum of 30 s; see below). Lower scores in the LFI reflect better physical function.

##### Hand grip strength

Patients will squeeze a hand-held, analogue, grip dynamometer as hard as possible for 2–3 s using their dominant hand. Patients will remain seated with their arm fully extended by their side throughout the test. The mean score from three trials will be recorded in kg.

##### Five-repetition sit to stand

Patients will begin seated in a firm, armless chair with both arms crossed against their chest. We will ask patients to position themselves on the edge of the chair seat to minimise trunk flexion [35] and instruct them to rise to a full standing position (legs straight) and then return to the seat (full weight on chair) five times, as quickly as they can whilst maintaining correct technique. A practice trial of one repetition will be given to check correct form, followed on by one test trial. The time it takes to complete five sit to stands will be recorded in seconds.

##### Balance

The balance test will involve patients standing unassisted with their feet placed side by side, semi-tandem, and tandem for a maximum of 10 s each. Recording will stop after 10 s or when the patient loses balance (i.e. steps out of position or grabs support). One trial will be performed in each stance position, with the time recorded in seconds.

##### Four-metre gait speed

Patients will walk at their usual pace for 4 m with the time recorded in seconds. Walking aids will be allowed if necessary.

#### Mid-upper arm circumference

The anthropometric measurement of mid-upper arm circumference is a valid measure of muscle mass in nonobese patients [36]. The measurement will be taken with a non-stretching measurement tape at the midpoint between the tip of the acromion and olecranon process of the dominant arm (to the nearest 0.1 cm). Patients will be in a sitting position with the dominant arm hanging relaxed during the measurements [36].

#### Physical activity

Physical activity will be objectively measured using an ActiGraph GT9X accelerometer worn on the nondominant wrist for at least 8 h per day over 7 days in the first and last weeks of the intervention. Daily total activity counts, steps, time spent sedentary, and time spent in light, moderate, and vigorous activity will be recorded. Freedson thresholds based on metabolic equivalents will be used to demarcate to intensity of physical activity: sedentary (≤ 100 counts/min), light (101–1951 counts/min), moderate (1952–5724 counts/min), and vigorous activity (≥ 5725 counts/min) [37, 38].

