**Methods:**

This is a protocol for a prospective, single-centre, single-arm, pretest-posttest feasibility trial. We aim to recruit 20 patients aged 60 years or older who have received treatment for HCC and are undergoing routine clinical monitoring. Patients will be invited to take part in two online, home-based, group exercise sessions per week for 10 consecutive weeks. The ‘virtual’ exercise sessions will be delivered in real time by an exercise professional through videoconferencing software. Each session will comprise 30 min of aerobic and resistance exercise performed at a moderate intensity, as guided by the 10-point Borg rating of perceived exertion scale. Feasibility outcomes include recruitment, retention, adherence, intervention fidelity, and safety. Acceptability of the intervention will be assessed using a mixed-methods approach via monthly online surveys and an exit telephone interview. Physical function, accelerometry-measured physical activity, mid-upper arm circumference, and patient-reported outcome measures (PROMS) will be assessed before and after the intervention to determine the feasibility of assessing outcome measures. Physical function outcomes include the short physical performance battery and Liver Frailty Index. PROMS include the Functional Assessment of Cancer Therapy-Hepatobiliary questionnaire, Functional Assessment of Chronic Illness Therapy-Fatigue questionnaire, Activities-specific Balance Confidence scale, Hospital Anxiety and Depression Scale, and the Godin Leisure-Time Exercise Questionnaire.

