### Exercise intervention

Patients will be invited to take part in two virtual exercise sessions per week for 10 weeks. Exercise sessions will comprise a maximum of 10 patients at any one time to allow for adequate safety monitoring and provision of individual feedback. Sessions will be delivered on weekdays in the late morning or early afternoon, which reflects patient preferences identified in our patient and public involvement (PPI) discussions and also avoids early morning exercise when exercise-induced adverse cardiovascular events are more frequent [27]. Exercise sessions will be separated by at least 48 h.

Exercise sessions will involve the option of chair-based or standing-based exercises (within the same session). Whether patients complete chair-based or standing exercises will depend on patient preference and functional ability (assessed by the research team); patients who take > 15 s to perform five sit to stands at baseline, show an inability to stand for 10 s in side by side/semi-tandem/tandem on baseline balance tests, self-report falling within the last 12 months, and/or score < 50% on the Activities-specific Balance Confidence scale (ABC scale), will be restricted to chair-based exercises in weeks 1–4 because of an increased risk of falls [28, 29]. A fall event is defined as ‘when you land on the floor or the ground, or fall and hit objects like stairs or pieces of furniture, by accident’ [30]. If a patient expresses a preference to change to standing or seated exercises after this period, they will be reassessed virtually and permitted to do so if they meet the requirements stated above. We will ask patients to nominate an emergency contact who we will contact if an adverse event occurs during the exercise sessions. In the case of an emergency, the research team will also contact emergency services and terminate the exercise session for all patients. Furthermore, we will encourage patients to have another person in the house when they are taking part in the scheduled exercise sessions, but if this is not possible, we will ask them to remotely ‘check in’ with their nominated contact after completing each exercise session. Patients will be required to have their cameras turned on and be visible during the exercise sessions so that they can be monitored for potential adverse events.

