Each exercise session will last 45 min and comprise of a 10 min warm up, 30 min of aerobic and resistance exercises, and a 5 min cool down involving static stretching. The exercises focus on multi-joint movements recruiting major muscle groups in the lower and upper body. The warm up will involve 5 min of a pulse-raising activity (such as seated pedalling) and 5 min of joint mobility exercises. Patients will then perform two sets of four aerobic exercises and two sets of four resistance exercise in a circuit-like manner. Each exercise will be performed for 60 s followed by 60 s of rest; this length of time was chosen to provide an adequate stimulus for adaptation but also provides patients enough time to prepare for the next exercise. Aerobic exercises will include exercises such as seated pedalling, high knee marching, step jacks, side steps, stepping forwards/backwards, and horizontal/vertical punches. Resistance exercises will use body weight and resistance bands as resistance and will include exercises such as chai rises, assisted lunges, horizontal rows, upright rows, overhead presses, wall press-ups, calf raises, rotations, and bicep curls. Each exercise can be modified to be performed in either a seated or standing position. The combination and sequencing of exercises will be varied between the two weekly sessions because our PPI discussions and previous research [20] suggest that older adults taking part in online exercise prefer some level of variation. An example exercise session is presented in Fig. 2.

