### Outcomes

The primary outcome for this study is feasibility of the exercise intervention and study procedures. Measures of physical function, mid-upper arm circumference, objectively measured physical activity, and PROMs will be assessed before and after the 10-week intervention to determine the feasibility of assessing outcome measures. Acceptability of the intervention will be assessed using a mixed-methods approach via monthly online surveys and an exit telephone interview (see Fig. 1).

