### Data and statistical analysis

#### Quantitative analysis

The flow of patients throughout the trial will be reported in a CONSORT flowchart. Descriptive statistics will be used to present baseline characteristics, feasibility outcomes, and acceptability survey responses. Continuous variables will be described with the mean and standard deviation (SD), and categorical variables will be reported as frequency and proportion. Continuous data with an asymmetrical distribution will be summarised with the median and interquartile range. A paired *t*-test or Wilcoxon signed-rank test (depending on data distribution) will be used to evaluate changes in outcomes from baseline to post-intervention, with the mean difference and 95% confidence interval from the model presented. Data will be analysed per protocol (i.e. missing data at follow-up will not be imputed).

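### Both accelerometer wear weeks fall inside the intervention, so the planned contrast is not the before/after change in physical activity that the protocol describes

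*Protocol article*

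**What the plan says.** Three parts of the protocol article describe this measure as a before/after assessment:

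- Abstract, Methods: accelerometry-measured physical activity is in the list of measures that "will be assessed before and after the intervention to determine the feasibility of assessing outcome measures".
- Outcomes: "objectively measured physical activity, and PROMs will be assessed before and after the 10-week intervention".
- Quantitative analysis: a paired t-test or Wilcoxon signed-rank test "will be used to evaluate changes in outcomes from baseline to post-intervention".

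The Physical activity section, which fixes the timing, has the device worn for a minimum of 8 hours daily "over 7 days in the first and last weeks of the intervention". It does not itself use the word baseline; that status comes from the other three places.

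On exposure, the Exercise intervention section states: "Patients will be invited to take part in two virtual exercise sessions per week for 10 weeks". It adds: "Each exercise session will last 45 min". Under Preparation procedures, the accelerometer is in the pack handed over at induction, and a one-to-one video session takes place before the programme starts. Neither step is tied to a wear period.

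**The concern.** Week 1 of the programme is an exposed week. Patients have sessions in it and already hold the resistance bands, the pedal exerciser and a diary in which they record daily steps. A value from that week cannot serve as a pre-intervention reference, and a value from the last week is not an after value either. Yet these two weeks are the only accelerometer data that the paired test could use.

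What is at stake is the meaning of the accelerometry result. The objectives include preliminary evidence of efficacy, and the Discussion says the outcome data will indicate how large and how variable effects may be, for use in designing the randomised trial. With a single arm, no control group can recover the missing contrast. The trial would also not test whether a pre-intervention wear week can be obtained, which a later trial using this measure before and after would need.

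**Working it through.** The protocol gives no expected change or SD for physical activity, so there is no stated figure to reproduce. The check is on timing, followed by simple arithmetic.

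**Timing.** Sessions run twice weekly for 10 weeks. The first and last weeks of the intervention are therefore both session weeks. This cannot be reconciled with before and after the intervention.

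**What the contrast measures.** Let P be weekly activity before the programme, W1 activity in the first week and W10 activity in the last week.

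- Change described: W10 − P
- Change the schedule delivers: W10 − W1
- Difference between them: W1 − P, the week-1 departure from the pre-programme level

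This identity does not depend on what the sessions contain.

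**Session time in a wear week.**

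- Sessions: 2 × 45 = 90 min
- Minimum wear: 8 h × 7 = 56 h = 3,360 min
- Share: 90 / 3,360 = 2.7%
- Timed circuit bouts only: 2 sets × (4 + 4) exercises × 60 s = 16 min per session, 32 min per week, or 32 / 3,360 = about 1%

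**Illustration in session minutes.** Let S = 90 min, let a1 and a10 be the proportions of sessions attended in the first and last weeks, let B be other activity gained by the last week, and let f be the share of B already present in week 1. Then:

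- True change = S·a10 + B
- Observed change = S·(a10 − a1) + B·(1 − f)
- Understatement = S·a1 + f·B

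Attendance of 70% is taken from the 14-of-20 threshold in Criteria for success. The ranges for B (0 to 60 min/week) and f (0 to 1) are assumptions.

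| a1, a10 | True change (min/week) | Observed (min/week) | Understated by (min/week) |
|---|---|---|---|
| 100%, 100% | 90 to 150 | 0 to 60 | 90 to 150 |
| 70%, 70% | 63 to 123 | 0 to 60 | 63 to 123 |
| 100%, 70% | 63 to 123 | −27 to 33 | 90 to 150 |
| 70%, 100% | 90 to 150 | 27 to 87 | 63 to 123 |

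With B = 0 and equal attendance in the two weeks, a wear week before session 1 would show 90 min/week at full attendance or 63 at 70%. The planned contrast shows 0 in both cases.

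**Direction.** If patients reduce other activity by C minutes in week 1 (with no other gain that week), then W1 − P = 90·a1 − C. This reaches zero at C = 90 with full attendance, or C = 63 at 70%. Beyond that, the planned contrast overstates the change.

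**The case against.** The strongest case on the other side is about importance. The primary outcome is feasibility. Physical activity is neither in Table 1 nor in the criteria for success. The stated reason for repeating these measures is to learn whether they can be collected, and wear compliance can be judged in weeks 1 and 10 too. FACT-Hep, not accelerometry, is the likely primary outcome of the later trial, and the Godin questionnaire is among the patient-reported measures planned before and after. All of this stands, and it limits the consequence. It does not remove the contradiction in timing.

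A reader might go further and infer that the whole direct effect of the sessions is lost. The document does not support that. Full cancellation needs equal attendance and equal session content in the two weeks. The Exercise intervention section describes progression guided by perceived exertion and restricts patients at higher risk of falls to chair-based work in weeks 1–4, so session activity can differ by the last week. Only the week-1 level is subtracted.

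A reader might also infer that the bias must run toward no change, or that a null result would mean nothing. The direction depends on how patients behave in week 1, and the last-week minus first-week difference still describes change over the course of the programme. Nor does any section say that accelerometer means or SDs will be carried forward as baseline values; the statements about effect size and variability are general.

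Finally, session time is a small part of wear time, and session minutes are not accelerometer counts. That is fair: the minutes show the mechanism and do not estimate the bias in the recorded outcome.

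**Conclusion.** The point holds as an internal contradiction with a real but limited effect. The wear schedule conflicts with the Abstract, the Outcomes section and the planned paired test, and no text shown supplies a pre-intervention accelerometer week. The planned difference misses the change described by the week-1 departure from pre-programme activity.

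If attendance is 70% to 100%, other activity rises by 0 to 60 min/week and there is no compensating reduction in week 1, the understatement is 63 to 150 min/week in session-time terms. The observed change can turn negative when attendance falls between the two weeks. The size in accelerometer counts cannot be derived from the document.

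The conclusion concerns accelerometry only and alters none of the success criteria. The study schedule (Fig. 1) is not shown and could not be checked. It might clarify the intended timing, but it would not remove the conflict within the text.

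**What to change.** 1. Take the first 7-day wear period after induction and before the first group session. The device is already issued at induction, so no extra device or visit is needed.
2. Keep the last-week wear period and label it as during the intervention.
3. Align the Abstract, Outcomes, Physical activity and Quantitative analysis sections, so that the paired contrast is named as pre-intervention against last week of the intervention.

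The cost is protocol wording and at least 7 days between induction and session 1. The new wear week would follow receipt of the equipment pack, so it precedes the sessions but not all contact with the study.

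Wearing the device in the week after session 20 is not an interchangeable alternative. Paired with a pre-session week, it would have no sessions in either window and would measure carry-over instead of activity during the programme. If that is the question of interest, the protocol should say so.

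If enrolment has begun, make the change prospectively and report week-1 data already collected as on-intervention values.
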